### Secondary analyses

#### Per-protocol analysis

A per-protocol analysis will be conducted excluding patients who were incompliant with the study protocol (ONS-prescription for < 80% of the days from inclusion to discharge), patients that were nil per os for > 10% of their meals during the time of intake monitoring, patients of which > 10% of meals could not be assessed during the time of intake monitoring, patients that did not receive the randomized intervention, and patients violating any eligibility criteria.

The same parameters and tests as in the primary analysis will be assessed and conducted for this population.

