### Study conduct and data collection

Participants are recruited consecutively. Based on routine screening upon admission, patients with an NRS 2002 total score of > 3 are referred to the RDs [25, 32]. The RDs check the eligibility criteria. If there is an indication but no ONS prescribed, the RDs counsel the patient concerning ONS. Once an eligible patient agrees to a prescription of ONS and an appropriate product is selected, the patient is informed by the RD about the possibility of participating in the trial. Upon approval, the RD obtains informed consent and randomizes the patient. The prescription of ONS is carried out by the medical doctors (MD). All involved personnel (MDs, nursing and catering staff) is informed by the RDs of the patient’s participation in the trial. An overview of the patients’ flow is given in Fig. 1 and an overview of the time schedule for participants is provided in Table 2. The trial is only concerned with ONS administration and has no influence on any other aspects of patients’ treatments. ONS may be discontinued if the indication therefore no longer exists.

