**Fig. 1 Fig1:**
[figure not shown]
Patients’ flow. NRS 2002, Nutritional Risk Screening 2002; ONS, oral nutritional supplement; RD, registered dietitian; SAE, serious adverse event

**Table 2 Tab2:** Time schedule for participants

Study period	Screening	Intervention period					Evaluation	Follow-up
Visit	1	2	3	4	5	6		
Day	0	1	8	15	22	29	*	**
NRS 2002 total score	x							
NRS 2002 subscore nutritional status	x							
Inclusion and exclusion criteria	x							
Information, informed consent	x							
Assignment to study group		x						
Baseline patient characteristics		x						
Energy intake/day (kcal)**		Continuous assessment						
Protein intake/day (g)**								
ONS intake/day (ml)**								
Serious adverse events (SAE)**								
Handgrip strength (kg)		x	x***	x***	x***	x***		
Body weight (kg)		x	x***	x***	x***	x***		
Body height (cm)		x						
BMI (kg/m^2^)		x						
Appetite (VAS)		x	x***	x***	x***	x***		
Nausea (VAS)		x	x***	x***	x***	x***		
Procedural variables							x	
Hospital LOS (d)							x	
30-day mortality (y/n)								x

*After patient dismissal or after 30 days of inclusion

**For 30 days upon inclusion

***Assessment at day 1, day 8, day 15, day 22, and day 29

Visits 2–6: study visits may be conducted earlier or later by a maximum of 2 days

The criteria for ONS discontinuation are:
ONS is not indicated anymore due to increased food intakeOccurrence of a serious adverse event (SAE) that necessitates a halt to the prescription

The reasons for discontinuation are documented. Furthermore, withdrawal from the trial is possible at any time at the patients’ request.

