### Measurements

#### Energy, protein, and ONS intake

All parameters are assessed continuously until discharge or for a maximum of 30 days (Table 2). The RDs calculate daily energy and protein requirements according to relevant current clinical nutrition guidelines that apply to the patients in the MEDPass Trial [10, 14, 33]. The formula per patient is chosen according to age and body mass index (BMI). As some patients may suffer from progressive renal failure, the Clinical Practice Guideline of the National Kidney Foundation is used to calculate these patients’ protein needs [34]. The formulas for daily energy requirements as related to the primary outcome are listed in Table 3.

**Table 3 Tab3:** Calculation of daily energy requirements

Formulas for daily energy requirements		
	BMI < 18.5 kg/m^2^	BMI > 18.5 kg/m^2^
< 65 years	Actual body weight × 30 kcal [10]	Actual body weight × 27 kcal [10]
> 65 years	Actual body weight × 32 kcal [14]	Actual body weight × 30 kcal [14, 33]

Recommended protein intake is calculated according to the guidelines for geriatric and medical patients using the formula 1 g/kg body weight/day [10, 14, 33]. However, patients with chronic kidney disease and estimated glomerular filtration rate (eGFR) < 30 mL/min/1.73m^2^, who are not on dialysis, are an exception. In this case, the actual body weight is multiplied by 0.8 g/kg body weight/day [34].

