#### Baseline patient characteristics and procedural variables

The following baseline patient characteristics are recorded by RDs during visit 1 (Table 2):
✓ Disease categories for main diagnosis (gastrointestinal disease, infectious disease, cardiovascular disease, neurological disease, oncologic disease, other diseases)✓ Department in which the patient is hospitalized✓ Gender (male, female)✓ Age (years)✓ Energy content per ml ONS (1.5 kcal/ml or 2 kcal/ml)✓ NRS 2002 total score✓ NRS 2002 subscore for impaired nutritional status✓ Body weight (kg)✓ Body height (cm)✓ BMI (kg/m^2^)

The following procedural variables are recorded after discharge by one of the co-investigators:
✓ Number of days from trial inclusion to hospital discharge✓ Number of days with prescribed ONS✓ Number of days with energy and protein intake monitoring✓ Compliance versus non-compliance with the study protocol✓ Number of meals at which patients were nil per os during energy and protein intake assessment (meals at which patients are not allowed to eat for medical reasons)✓ Number of meals at which food intake could not be assessed✓ Involvement of RDs in the treatment of the patients

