#### Primary analysis

The baseline patient characteristics will be summarized for both groups. The primary analysis will be performed as an intention-to-treat (ITT) analysis including all randomized patients regardless of protocol adherence. In a further step, we will also do a per-protocol analysis excluding patients with major protocol violations as outlined below.

For the primary outcome, we will test whether MEDPass administration is superior to usual care and compare the average amount of daily energy intake using a Student’s *t* test or chi-square test. We will also fit linear regression models adjusted for initial NRS 2002 score and average amount of energy in the ONS, reported adjusted differences (coefficients), and corresponding 95% confidence intervals (CIs). Total energy, protein, and ONS intake throughout the study period will be divided by days of assessment per patient. Linear regression analysis adjusted for stratification factors will also be used for the evaluation of average daily protein intake as compared to the individual requirement (%) throughout the hospitalization, average intake of ONS/day (ml) throughout the hospitalization, and hospital LOS (days) between the groups. Logistic regression analysis adjusted for stratification factors will be is used for difference in 30-day mortality (yes/no) between the groups. Repeated measure models will be used for the evaluation of differences in course of handgrip strength throughout the hospitalization, weight changes throughout the hospitalization, and course of appetite and nausea throughout the hospitalization. The procedural variables will be analyzed and presented descriptively. There will not be a statistical safety assessment since there are no safety endpoints in the MEDPass Trial. Safety events will be presented descriptively.

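### The per-protocol rule has no exception for ONS stops that the protocol itself permits, so exclusion from the per-protocol set can depend on the primary outcome

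*Protocol article*

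**What the plan says.** Two parts of the protocol article bear on this point.

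- **Stopping ONS.** The section on study conduct and data collection states that "ONS may be discontinued if the indication therefore no longer exists". The list of criteria below Table 2 gives two grounds: ONS is no longer needed because the patient eats more, or a serious adverse event (SAE) makes it necessary to halt the prescription. It adds: "The reasons for discontinuation are documented".
- **The per-protocol set.** The primary analysis section announces a "per-protocol analysis excluding patients with major protocol violations as outlined below". The per-protocol section then names as incompliant those with "ONS-prescription for < 80% of the days from inclusion to discharge". No exception is given for stops that meet the criteria. The same outcomes and tests as in the primary analysis are to be applied to this set.

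The section on baseline and procedural variables lists the two counts that the rule needs: "Number of days with prescribed ONS" and "Number of days from trial inclusion to hospital discharge". On the period of intake measurement, the Measurements section says: "All parameters are assessed continuously until discharge or for a maximum of 30 days".

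**The concern.** The same event is correct conduct in one section and a major violation in another. If this were only a matter of labels it would be trivial. However, the first permitted reason for stopping is increased food intake, and food intake is a component of the primary outcome, average daily energy intake. Membership of the per-protocol set can then depend on something that happens after randomization and is linked to the result being compared.

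Two features of the design add to this. The trial is open-label, so those who decide on stopping know the allocation. Control prescriptions are unstandardized, so stopping practice may differ between arms. At stake is how the per-protocol result is read beside the intention-to-treat result: a gap between the two could come from the selection rule and not from adherence.

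**Working it through.** **1. The plan's own figures.** Inputs from the sample size section: means of 2000 and 2200 kcal/day, SD 500, alpha 0.05 (taken as two-sided), power 80%. Per arm, n = 2 × (1.960 + 0.842)² × 500² / 200² = 98.1, hence 99, or 198 in total. The stated 200 is reproduced; 100 per arm gives 80.7% power. These inputs are sound for an illustration.

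**2. Who the 80% rule removes.** Prescribed days divided by days from inclusion to discharge:

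| Stay (days) | Excluded with | Kept with |
|---|---|---|
| 10 | 7 or fewer (7/10 = 70.0%) | 8 or more (8/10 = 80.0%) |
| 14 | 11 or fewer (11/14 = 78.6%) | 12 or more (12/14 = 85.7%) |
| 21 | 16 or fewer (16/21 = 76.2%) | 17 or more (17/21 = 81.0%) |

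A permitted stop leads to exclusion only if it leaves more than 20% of the stay without a prescription. Under the text as written, such a patient is then excluded whatever the reason for the stop.

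**3. Direction of the bias (illustration only).** The article gives no stopping rates, so the following are assumptions. Intake is normal with the planned means and SD. A patient with average intake above a cut-off c is stopped early enough to be excluded with probability p. With z = (c − μ)/σ and P = 1 − Φ(z), the mean of those who remain is

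μ − pσφ(z) / (1 − pP).

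For c = 2200 and p = 0.5 in both arms:

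- MEDPass: z = 0, P = 0.500, φ = 0.3989. Shift = 0.5 × 500 × 0.3989 / 0.750 = 133.0. Excluded: 25.0%.
- Control: z = 0.4, P = 0.3446, φ = 0.3683. Shift = 0.5 × 500 × 0.3683 / 0.8277 = 111.2. Excluded: 17.2%.
- Difference: 200 − 133.0 + 111.2 = 178 kcal/day.

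Other assumed values, from the same formula:

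| True difference | Cut-off | p MEDPass / control | Per-protocol difference (kcal/day) |
|---|---|---|---|
| 200 | 2200 | 0.25 / 0.25 | 193 |
| 200 | 2200 | 1 / 1 | 82 |
| 200 | 2500 | 0.25 / 0.25 | 187 |
| 200 | 2500 | 0.5 / 0.5 | 169 |
| 200 | 2500 | 1 / 1 | 114 |
| 200 | 2200 | 0.25 / 0.5 | 254 |
| 200 | 2200 | 0.5 / 0.25 | 117 |
| 0 | 2200 | 0.5 / 0.5 | 0 |
| 0 | 2200 | 0.5 / 0.25 | −61 |
| 0 | 2200 | 0.25 / 0.5 | +61 |

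A common rule shrinks a true effect and creates none where there is none. Unequal stopping can move the estimate up or down.

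**4. A weaker link to the outcome.** Step 3 lets the stop depend on the outcome itself. If the trigger only correlates with average intake at r (same means and SD), each shift is multiplied by r. For c = 2200, p = 0.5 and r = 0.5, the difference is 200 − 0.5 × (133.0 − 111.2) = 189 kcal/day.

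**The case against.** - **The trigger is not the outcome.** Stopping follows food intake at one moment. The primary outcome is total intake, food plus ONS, averaged over all assessed days and related to requirement. A patient who stops also loses the ONS energy afterwards and need not have a high average. This stands. It is why a claim that the rule removes the successes, or a fixed percentage of attenuation, would go beyond the document. It weakens the link to the outcome but does not remove it.
- **Not every permitted stop excludes.** This stands, as the table of stays shows. A late stop leaves the patient in the set.
- **A minimum-exposure rule is a legitimate per-protocol choice.** This stands in part. A sponsor may want only patients with substantial exposure, but should then say so and not describe permitted management as non-compliance and a major violation.
- **The analysis plan may settle it.** Handling of permitted stops could be refined there. The article, however, fixes the threshold and the denominator explicitly, and the point concerns what is stated.
- **The day-30 window.** A reader might infer that fully adherent long-stay patients fail the rule, since 30/38 = 78.9% (and 30/37 = 81.1%). That requires ONS days counted only to day 30 against a denominator running to discharge, which no section states. Prescriptions are in the electronic record and could be counted to discharge. The footnote to Table 2 places the procedural variables after discharge or after 30 days, which may cap both counts. The document does not support that inference. What remains is an unclear window.

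**Conclusion.** The point holds as an inconsistency within the stated plan. The per-protocol rule classes as a violator a patient whose ONS was stopped on a ground that the protocol lists, once fewer than 80% of days are prescribed. Stops for an SAE are caught in the same way. Because one listed ground is increased food intake, the secondary per-protocol comparison is open to selection on the outcome.

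The direction depends on stopping behaviour: toward zero with a true effect and a common rule in both arms, either way if the arms differ. The size cannot be derived, because the article gives neither stopping rates nor a distribution of stay. The figures above show a mechanism under assumed probabilities and are not estimates for this trial.

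A reader might also infer that the trial's main conclusion is at risk. It is not: the primary analysis is by intention to treat on all randomized patients, and neither it nor the sample size uses the 80% rule. The correction is worth making because it is small, but it concerns a secondary analysis.

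**What to change.** Reconcile the discontinuation criteria with the per-protocol definition in the analysis set only; no clinical rule needs to change. Suggested wording for the compliance criterion: *ONS prescribed on fewer than 80% of days from inclusion to the earliest of discharge, day 30, or a documented discontinuation that meets the protocol's criteria.* Days after a permitted stop then do not count as non-compliance.

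Keep the 80% rule as now written as a sensitivity analysis, and report exclusions by arm and by reason.

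As a minor alignment, count both prescribed days and total days over the intake-monitoring period, that is, inclusion to discharge or day 30, whichever is earlier. The exclusions for fasting and for unassessed meals in the same section already refer to that period.

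Cost: one sentence and one extra table row, using day counts and stopping reasons that are already collected. The trial status section reports ongoing recruitment (126 participants), so the change could be fixed before analysis. The downside is that some briefly exposed patients stay in the per-protocol set. A patient with two ONS days in a 20-day stay would count as compliant after a permitted stop. The sensitivity analysis shows whether this matters.

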#### Subgroup analyses

Subgroup analyses on the ITT patient set will include mean energy and mean protein intake throughout the hospitalization as compared to requirements. Linear regression will be used and adjusted for stratification factors to enable comparison of patients by group of different ONS energy content, different NRS 2002 subscore for nutritional status, different levels of appetite and different levels of nausea on day 1, different levels of handgrip strength at day 1, and different levels of dietetic involvement in patients’ nutritional care.

## Trial status

Recruitment is ongoing since November 22, 2018. As of September 8, 2020, 126 participants have been recruited. Expected completion of recruitment according to current projection is November 2021. The trial is conducted according to the protocol version 1.2 of November 22, 2019.

## Dissemination policy

The plans for the dissemination of the MEDPass Trial results include a publication in an international peer-reviewed journal, a poster presentation at one of the renowned nutrition congresses such as ESPEN or NUTRITION and the implementation of the results in the BSc curriculum of Nutrition and Dietetics at Bern University of Applied Sciences.

## Discussion

The MEDPass Trial studies a broad spectrum of patients at nutritional risk. This approach was chosen deliberately to ensure representability of the results on polymorbid patient populations of general medical and geriatric departments. The MEDPass Trial falls under the category of effectiveness research [37]. Effectiveness research aims at broadly representing the studied patient population and compares interventions to usual clinical practice [37]. Thus, the results of effectiveness research support clinical decision making and may improve the quality, effectiveness, and efficiency of health care [37]. A representative patient population as studied in the MEDPass Trial may more efficiently support decision making for the ONS administration mode.

Although the polymorbid, frail patient population accounts for the majority of healthcare costs, it is the least studied population [38]. Polymorbid patients are most often excluded from RCTs because of the complexity of their health condition [38].

To our knowledge, the MEDPass Trial is the first RCT in which total energy and protein intake of subjects with MEDPass versus conventional ONS administration are studied consistently and systematically throughout their hospitalization. Thus, the MEDPass Trial will answer the clinically relevant question if the MEDPass mode of administration is superior to the conventional administration of ONS concerning total energy intake of patients. Furthermore, it may help clinicians in their decisions on administration mode for clinical practice.

As in any open-label trial, there is potential for performance bias, as patients may be influenced by their trial participation [39]. Compliance with ONS and nutritional therapy may thus be increased [39]. In the MEDPass Trial, blinding of participants is not feasible due to the obviously different times of ONS administration. However, the recalculation of all meals by a fully blinded co-investigator enhances objectivity, promotes data quality, and minimizes bias.

The stratification of randomization is aimed at preventing statistical differences between groups due to ONS energy density. This is a relevant approach since differences between groups would directly affect the primary outcome. Furthermore, the stratification for NRS 2002 score is aimed at reducing differences in nutritional risk between groups. This may reduce bias significantly and therefore all statistics will be adjusted for both stratification factors. The wide selection of ONS available in the institution represents daily clinical practice. There is no influence of the financial sponsor on the selection of ONS in this study.

Our initial calculation and projections predicted the completion of patient recruitment in spring 2020. In the course of the trial, recruiting was prolonged for various reasons, including predominantly organizational barriers to recruitment. Organizational barriers are frequently described as significant for the prolongation of clinical trials [40–42]. In patients with unscheduled admissions, such as the majority of those in our facility’s medical department, recruitment challenges are more evident. LOS in the medical department is usually shorter than on the geriatric wards. This disqualifies some of the medical patients because after screening and referral, they may not stay three more days as needed according to the eligibility criteria. Moreover, medical patients with unscheduled hospitalizations may be too anxious about their treatment, in pain, or too unwell to provide consent [42]. Recruitment on the geriatric wards also presents challenges. Reading and understanding the consent forms may be difficult for some of the patients [41]. Furthermore, distrust and/or fatigue are known barriers in recruiting elderly patients onto clinical trials [41].

To facilitate recruitment, Kadam et al. as well as Huang et al. suggest reducing the complexity and interprofessional dependencies in trial setups [43, 44]. As the management of malnutrition is a highly interprofessional task, possibilities for reduction of complexity are scarce. Retrospectively, one option may have been to task the RDs to conduct the nutritional screening. In that scenario, the whole process from screening to patient information to inclusion would have been in the hands of the RDs. This may have proved more efficient as interprofessional dependencies would be reduced. 86% of clinical trials do not reach their recruitment targets in the projected time [43]. As personal resources of all involved professions in the MEDPass Trial are limited, prolonging the recruitment period to reach the desired power was the obvious course of action.

## Data Availability

The datasets used and/or analyzed during the current study are available from the corresponding author on reasonable request and with permission of all authors.

## Abbreviations

BMI: Body mass index
CEC: Competent Ethics Committee
CTU: Clinical Trial Unit
DRM: Disease-related malnutrition
EHR: Electronic health record
ESPEN: European Society of Clinical Nutrition and Metabolism
GCP: Good Clinical Practice
ITT: Intention-to-treat
LOS: Length of stay
MD: Medical doctor
NRS 2002: Nutritional Risk Screening
ONS: Oral nutritional supplements
PN: Parenteral nutrition
REDCap®: Research Electronic Data Capture
RCT: Randomized controlled trial
RD: Registered dietitian
RN: Registered nurse
SAE: Serious adverse event
TMF: Trial Master File
VAS: Visual analog scale
